### Clinical trial registration and registration date

The study is ongoing and was registered under ClinicalTrial.gov NCT04746261 on 2020-10-15 (https://clinicaltrials.gov/ct2/show/ NCT04746261), version 2, 2023-02-21. Further details are available on ClinicalTrials.gov under trial ID NCT04746261.

### Participants

Patients are recruited from diverse psychiatric healthcare settings, including psychiatric and emergency care, consultation psychiatry, inpatient psychiatric wards, and outpatient psychiatric care in Sweden. Those meeting the specified eligibility criteria (see below) are invited to participate in an initial visit. Ahead of the first visit, patients are provided with written information delineating the research project’s purpose, followed by a verbal description of its implications. All participant data will be kept in the REDcap system and in fire-safe locked cabinets at the research unit to ensure participant confidentiality. All data will be presented at group level so that no individual can be identified.

The study is currently recruiting.

### Eligibility criteria

Inclusion criteria

Age ≥ 18 years.Recent contact with psychiatric healthcare following a suicide attempt within the three months preceding the first visit.Scheduled meeting or appointment with a designated healthcare provider at a specific psychiatry or primary care unit after the initial visit to the study center.

Exclusion criteria

Current psychosis featuring active delusions, hallucinations, or negative symptoms likely to impact therapy.Diagnosis of emotionally unstable personality disorder (ICD 10) as documented in the medical record.Inability to undergo therapy without the assistance of an interpreter.Intellectual disability, dementia, or any other condition impeding the comprehension of the study’s implications and hindering the provision of informed consent.

### Therapists

All therapists are experienced clinicians (psychologists, nurses, or social workers) at psychiatric services with a varying extent of prior training in psychotherapeutic techniques. All have experience of working with suicidal individuals. The ASSIP training includes two days of theoretical lectures and skills training as well as video examples. To become a certified ASSIP therapist, the trainee needs to complete five case treatments under supervision, all of which must be approved. The teachers and supervisors are the creators of the method or have been trained by the creators. Yet uncertified therapists who have full supervision may treat patients in the RCT.

### Interventions

The interventions being studied are ASSIP (described above in the background section) plus treatment as usual (TAU) or TAU only. TAU after a suicide attempt varies and is typically based on diagnosis, individual needs, and local healthcare routines. It may involve contact with primary care or specialized psychiatric services and various types of treatments such as pharmacological treatment, psychotherapy, or other interventions. For details of the interventions, see Table 1.

**Table 1 Tab1:** Procedures for participants randomized to treatment as usual plus ASSIP

	Session 1	Session 2	Session 3	3 months after visit 3	6 months after visit 3	9 months after visit 3	12 months after visit 3	18 months after visit 3	24 months after visit 3
*Video recording of the session	X								
*Narrative interview	X								
*Video playback		X							
*Home assignment, either visit 1 or 2	X	X							
*Safety plan and Leporello**			X						
WAI-SR			X						
*Send standardized letters				X	X	X	X	X	X
Follow up according to the flow chart for all study participants				X			X		X

### Standardized evaluation forms for data collection

Throughout the project, a research evaluation is conducted during the initial baseline visit prior to randomization. These evaluations utilize:

The Suicide Intention Scale (SIS) [23] is used to measure the severity of a specific suicide attempt. It assesses the intent behind the attempt, including factors such as planning, lethality, and perceived seriousness.Columbia-Suicide-Severity-Rating Scale (C-SSRS) [24] is a comprehensive tool used to assess past and recent suicidal ideation, behaviors, and actual suicide attempts. It evaluates the intensity and frequency of suicidal thoughts, as well as the presence of suicide plans and actual suicidal behavior. This scale provides a standardized method to assess suicide risk and monitor changes over time.Mini International Neuropsychiatric Interview (MINI)version 7.0.1 [25] is a structured diagnostic interview used for psychiatric assessments. It covers a wide range of mental disorders, including mood disorders, anxiety disorders, psychotic disorders, and substance use disorders. The MINI provides a standardized approach to diagnosis, allowing clinicians to identify psychiatric conditions based on established criteria.The Interview Schedule for Social Interaction (ISSI) [26] is a tool used to assess an individual’s social interaction patterns and skills through structured interviews. It evaluates various aspects of social interaction, such as communication, empathy, and assertiveness.AUDIT (Alcohol Use Disorders Identification Test) and DUDIT (Drug Use Disorders Identification Test) [27] are screening tools designed to identify individuals at risk of alcohol or drug-related problems. They consist of a series of questions assessing the frequency and intensity of alcohol or drug use, as well as related consequences.The Life Events Checklist for DSM-5 (LEC-5) [28] is a self-report measure used in assessing exposure to traumatic events according to the criteria of the Diagnostic and Statistical Manual of Mental Disorders (DSM-5). It helps clinicians or researchers gather information about various traumatic experiences a person may have encountered.The EuroQol 5-Dimension 5-Level (EQ-5D-5 L) [29] questionnaire is a standardized instrument for measuring health-related quality of life. It assesses five dimensions of health (mobility, self-care, usual activities, pain/discomfort, and anxiety/depression) using both descriptive items and a visual analog scale.The Montgomery-Åsberg Depression Rating Scale-Self Report (MADRS-S) [30] is a self-report measure used to assess the severity of depression symptoms. It consists of items that evaluate mood, vegetative symptoms, and cognitive symptoms commonly associated with depression.The Internalized Stigma of Mental Illness (ISMI) [31] self-report scale measures the degree to which individuals with mental illness internalize stigma. It assesses various aspects of self-stigmatization, including alienation, stereotype endorsement, perceived discrimination, social withdrawal, and stigma resistance.The COPE (Coping Orientation to Problems Experienced) self-report inventory [32] is a questionnaire designed to assess coping strategies used by individuals when dealing with stress or challenging situations. It measures various coping styles, such as problem-focused coping, emotion-focused coping, and avoidance coping.

The assessment is carried out by researchers associated with the project. The SIS, CSSR-S, and MINI assessments at the baseline visit are carried out by a specialist or resident in psychiatry. A trained research nurse with experience in clinical psychiatry conducts all other evaluations. These assessment tools provide a structured framework.

### Health encounters during the study

In addition, the study ensures that all participants have, see Table 2:

**Table 2 Tab2:** Study procedures, all participants in the ASSIP RCT

	Baseline visit	3 months after the baseline visit	12 months after the baseline visit	24 months after the baseline visit	
Signing of the informed consent	X				
Demographic data*	X				
Background information*	X				
MINI 7.0.1	X				
C-SSRS	X	X	X	X	
SIS	X				
AUDIT self-report	X				
DUDIT** self-report	X				
LEC-5 self-report	X				
ISSI*** self-report	X	X	X	X	
EQ-5D-5 L*** self-report	X	X	X	X	
MADRS-S*** self-report	X	X	X	X	
ISMI*** self-report	X	X	X	X	ISMI*** self-report
COPE*** self-report	X				
Randomization to ASSIP + TAU or only TAU****	X				
Structured telephone interview according to the follow-up interview template		X	X	X	

*According to the interview template and self-report template

**For patients who answered yes in the interview regarding drugs

***Sent home by mail for follow-up at month 3, 12 och 24

****Patients who are randomized to ASSIP see “flow chart ASSIP therapy”

scheduled follow-up healthcare engagement subsequent to the baseline visit.are contacted for follow-up sessions administered by a research nurse at 3, 12, and 24 months. These may include suicide prevention interventions as a precautionary measure to safeguard patient well-being.

While these are data points included in the research study (as described below baseline visits and follow-up visits), they also represent a minimal equivalent intervention that both groups receive, involving initial contact and basic follow-up.

### Study procedures

#### Baseline assessment

During the baseline visit, research interviews are administered by members of the research team, comprising a specialist or resident physician in psychiatry and an experienced mental health professional with clinical expertise in the targeted patient group. The research interview adheres to a structured interview protocol designed to systematically elicit information about various background factors, including but not limited to marital status, educational background, employment status, sick leave history, prior treatments, and healthcare contacts.

After the interview, the patient is randomized to either receive usual treatment plus ASSIP or only usual treatment, and the information about group assignment is provided to the patient in connection with the baseline visit, along with information about the appointment with the ASSIP therapist.

#### Outcomes

To assess the primary outcome variable of new suicide attempts, multiple data sources will be employed, and in the primary analyses, a comprehensive approach will be taken, combining data from patient reports via telephone interviews (including C-SSRS), medical charts, and registers. A participant will be considered to have a new attempt based on data from any source including lethal suicide attempts. The secondary outcome is suicidal ideation within the same time frames after study inclusion. Suicidal ideation is defined as MADRS-S item 9 ≥ 4 on self-assessment. All study participants undergo follow-up assessments at 3 months, 12 months, and 24 months after the initial visit through structured telephone interviews conducted by experienced healthcare professionals. During these follow-ups, details of treatments and interventions since the previous visit are recorded. In cases where ongoing suicidal ideation is detected, standard healthcare procedures are implemented to manage the situation within the established protocols. Follow-up assessors and outcome assessors are blinded. However, as the intervention is a psychotherapeutic treatment, it is obvious to participants and therapists that they are receiving the intervention and are therefore not blinded. No formal Data Monitoring Committee (DMC) will be involved in this trial as the REDCap system was considered adequate.The research team, including the principal investigators, will conduct periodic interim analyses to monitor the safety and effectiveness of the intervention. The research team will systematically monitor and document any adverse events throughout the trial. This trial does not include an external auditing process. The research team will ensure adherence to the protocol through internal monitoring and oversight. Regular meetings will be held to review study progress, data collection, and adherence to ethical and procedural standards.

To provide a comprehensive understanding of TAU, medical chart data are collected for the periods two years before and two years after the index suicide attempt.

Register data linked by personal identification number are compiled two years after the index/baseline from several sources, including:

The National Board of Health and Welfare’s Cause of Death Register: Data regarding suicide mortality.Patient Register: Offering comprehensive information on inpatient and specialist healthcare utilization and diagnoses.Prescription Drug Register: Detailing purchases of prescribed medications for the study participants.Statistics Sweden (SCB): Longitudinal Integrated Database for Health Insurance and Labor Market Studies (LISA): Furnishing socio-economic and labor market-related data.

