### Mapping of treatment as usual

TAU is mapped through telephone interviews and journal reviews using a specific template and recorded in REDCap. The mapping includes ICD-10 diagnoses, healthcare contacts, pharmacological and psychotherapeutic treatments, as well as other interventions.

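### Assessors are stated to be blinded, but the calls that supply interview-based attempts also ask unblinded participants which treatments they received, so that source is at high risk of unblinding

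*Protocol article*

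**What the plan says.** The Outcomes section of the protocol article makes a positive claim: "Follow-up assessors and outcome assessors are blinded". It then concedes of the other parties that "it is obvious to participants and therapists that they are receiving the intervention and are therefore not blinded".

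The primary outcome, a new suicide attempt, is built by "combining data from patient reports via telephone interviews (including C-SSRS), medical charts, and registers". The rule is inclusive: "A participant will be considered to have a new attempt based on data from any source including lethal suicide attempts".

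On the content of the 3-, 12- and 24-month telephone interviews, the same section says: "During these follow-ups, details of treatments and interventions since the previous visit are recorded". Mapping of treatment as usual agrees: "TAU is mapped through telephone interviews and journal reviews using a specific template and recorded in REDCap". It lists psychotherapeutic treatments and other interventions among the items mapped. Health encounters during the study describes these contacts as "follow-up sessions administered by a research nurse at 3, 12, and 24 months".

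The only other masking statement is in Study design and data management, where the electronic randomisation is said to be blinded to the data handler.

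**The concern.** ASSIP is a psychotherapeutic treatment of three sessions followed by letters over two years. An interviewer who asks a participant in the ASSIP arm which treatments and interventions they have had is likely to hear about it. That interviewer is described as blinded and also collects the C-SSRS attempt data. The article therefore claims a property that its own procedure undermines.

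The classification is open to influence. Study design and data management defines an attempt through evidence of intent to die, and that evidence may be only implied. Deciding whether a reported episode counts is a judgement, and knowing the arm can sway it. Because one positive source is enough, a call made at interview enters the primary outcome directly. At stake is a shift in recorded attempts in one arm that the chi-square test would read as a treatment effect, or that would hide one.

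**Working it through.** **1. The statements side by side**

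| Element | Where | What it implies |
|---|---|---|
| Assessors blinded | Outcomes | The interviewer should not know the arm when scoring attempts |
| Treatments recorded at the same calls | Outcomes | The interviewer asks for information that can reveal the arm |
| Calls map psychotherapy and other interventions | Mapping of treatment as usual | ASSIP falls within the question |
| Participants not blinded | Outcomes | The respondent can reveal the arm |
| Interview, chart, register; any one suffices | Outcomes | The interview can decide a participant's status alone |

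**2. When the interviewer could learn the arm**

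- At any call where treatment is asked before the attempt items.
- At months 12 and 24, even with attempt items first, if the interviewer made the earlier call or can see its treatment answers.
- Not through the registers (Patient Register, Cause of Death Register), which are compiled independently of the study's assessors.
- Through charts only if ASSIP contacts are written there. This is plausible, since Therapists says ASSIP is delivered by clinicians at psychiatric services, but it is not stated.

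**3. The plan's own figure**

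Power calculation: 10% v 20%, alpha 0.05, power 0.8, 199 per group. With pooled variance under the null, two-sided, no continuity correction:

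n = [1.960·√(2·0.15·0.85) + 0.842·√(0.10·0.90 + 0.20·0.80)]² / 0.10² = (0.990 + 0.421)² / 0.01 ≈ 199.

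The stated figure reproduces, so 199 per arm is used below.

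**4. Illustration: no true effect (bias size assumed)**

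Both arms are truly at 20%, the plan's rate for conventional treatment. A share m of all ASSIP-arm events is not recorded, so the recorded ASSIP rate is p = 0.20(1 − m). With d = 0.20 − p, p̄ the mean of the two rates, SE₀ = √(2p̄(1 − p̄)/199) and SE₁ = √([0.16 + p(1 − p)]/199):

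P(reject) = Φ((d − 1.96·SE₀)/SE₁) + Φ((−d − 1.96·SE₀)/SE₁).

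For m = 10%: p = 0.18, SE₀ = 0.0393, SE₁ = 0.0393; Φ(−1.45) + Φ(−2.47) = 0.073 + 0.007 = 0.080.

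| m | Recorded ASSIP rate | Reject, favouring ASSIP | Reject, two-sided |
|---|---|---|---|
| 0 | 20% | 2.5% | 5.0% |
| 5% | 19% | 4.4% | 5.7% |
| 10% | 18% | 7.3% | 8.0% |
| 20% | 16% | 17.8% | 17.9% |

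**5. Effect of the other sources**

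An interviewer cannot suppress an event that a chart or register also shows. If only a share s of ASSIP-arm events depends on the interview, the overall loss is s·m. The Background estimates that about half of suicide attempts in Sweden receive hospital care. Taking s = 0.5 (an assumption for this sample), 10% or 20% under-recording of interview-only events is 5% or 10% overall. Rejection is then 5.7% or 8.0%.

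**6. The opposite direction**

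If ASSIP-arm events are over-recorded under the planned 10% v 20%, the recorded ASSIP rate is 11% (10% over-count) or 12% (20% over-count). Power falls from 80% to 70% or 59%.

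**The case against.** The strongest defence is that a journal article condenses a fuller protocol. Question order, separate staff, instructions to participants and masked adjudication are details it may leave out, and the follow-up template is not shown. Delivery of each ASSIP component is recorded separately (Mapping the implementation of ASSIP), so the call need not ask about ASSIP. Usual treatment can itself include psychotherapy (Interventions), so hearing of therapy alone does not give the arm away. All of this stands. It is why the conclusion is a high risk of unblinding in one source, not proof that blinding fails. It does not remove the point, because the article states both the blinding and the procedure that works against it.

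Three stronger readings are tempting, and the article does not support them:

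- *That ascertainment of the primary outcome as a whole is not blind.* Register data do not depend on the assessors, and the any-source rule limits what an interviewer can under-record.
- *That chart reviewers see ASSIP notes while looking for attempts.* Charts serve both outcome ascertainment and the mapping of usual treatment, but the article does not say who reads them or whether ASSIP contacts appear there.
- *That the follow-up nurse learned the arm at baseline.* Baseline assessment says only that "information about group assignment is provided to the patient in connection with the baseline visit". Research nurses work at baseline and at follow-up, but nothing says that the same person does both, or that the nurse is present when allocation is disclosed. Whether one interviewer makes all three calls is also not stated.

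**Conclusion.** The concern holds for the interview source. The article claims blinded assessment, while the interviews behind one of the three primary-outcome sources also collect treatment information that can reveal the arm. For charts the risk is conditional on ASSIP contacts being recorded there; for registers it does not arise.

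Neither the size nor the direction of bias can be derived from the document. The rejection rates of about 8% and 18% assume 199 per arm, no true effect, 20% risk, and a loss of 10% or 20% of all ASSIP-arm events. They are smaller where other sources recover the events, and over-recording would cost power instead. This should be corrected: the risk bears on the primary outcome, is inexpensive to reduce, and the article reports that recruitment is still under way.

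**What to change.** - In REDCap, complete and lock the C-SSRS and attempt items at each call before the treatment section opens.
- Hide earlier treatment answers from whoever makes the later calls.
- Ask participants not to name ASSIP during the call; its delivery is already captured elsewhere. Log any unblinding that occurs.
- Classify chart episodes from an extract in which references to ASSIP are masked.
- Add a sensitivity analysis of the primary outcome in all randomised participants using only the Patient Register and the Cause of Death Register, both already planned.
- State in the protocol who is blinded to what. If these steps cannot be taken, restate the blinding claim as limited to the register source.

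**Cost.** The forms must be re-ordered and a masking step added. The register-only analysis has fewer events. If registers caught half of them (assumed, 5% v 10%), power would be about 47% at 199 per arm and 53% at 230 per arm (460/2), so it is a supporting check and not a decisive one.

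Moving the treatment history to post, or to after the month-24 attempt items, would separate the two tasks further. It would also weaken the mapping of usual treatment, whose content the Background names as something that needs study. That is a trade-off for the sponsor, and the steps above do not require it.

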### Study design and data management

The study is an RCT. Patients are randomized to either receive ASSIP + usual treatment or only usual treatment. The project employs stratified randomization based on the study site, ensuring that 50% of patients receive ASSIP at all sites. Randomization occurs electronically at the end of visit 1 via REDCap and is blinded to the data handler. REDCap is an electronic data capture tool [21] hosted at Lund University which will be used to manage data collection. The participating regions will collectively recruit a total of up to 460 patients who have recently attempted suicide. For this study, a suicide attempt is operationally defined as a self-inflicted, potentially harmful behavior exhibiting explicit or implicit evidence of the individual’s intent to die [22].

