### Power calculation

Based on Swiss findings regarding the effect of ASSIP [17], we anticipate that 10% of individuals in the group receiving ASSIP plus conventional treatment, and 20% of individuals receiving conventional treatment alone, will attempt suicide again during the follow-up period. According to the chi-square test, 199 individuals are required in each group to achieve a significant difference with a power of 0.8 and an alpha value of 0.05. Assuming a 15% dropout rate among patients, 460 patients need to be recruited. If the dropout rate is lower, fewer patients will suffice.

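### Repeated effectiveness analyses by the trial team itself, with no DMC, leave the 0.05 level and the assessors' blinding unprotected

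*Protocol article*

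**What the plan says.** The Outcomes section assigns interim work to the people running the trial: "The research team, including the principal investigators, will conduct periodic interim analyses to monitor the safety and effectiveness of the intervention". Just before this it rules out independent monitoring: "No formal Data Monitoring Committee (DMC) will be involved in this trial as the REDCap system was considered adequate". The same section excludes external auditing and states that those who do follow-up and outcome assessment are blinded.

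The Power calculation section gives one error level for one test: "199 individuals are required in each group to achieve a significant difference with a power of 0.8 and an alpha value of 0.05". Statistical considerations names the chi-square test for the main outcome.

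On the final number, Study design and data management says "The participating regions will collectively recruit a total of up to 460 patients", and Power calculation adds "If the dropout rate is lower, fewer patients will suffice".

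Reporting and publication plan schedules a first main-outcome paper once the last participant has one year of follow-up, although follow-up runs to 24 months.

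**The concern.** The article does not spell out that the looks compare arms. But its only efficacy question compares ASSIP plus usual care with usual care alone, so monitoring effectiveness can hardly mean anything else.

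Three things then combine:

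- The people looking are the trial team, while recruitment is still open.
- Nothing independent stands between the results and trial conduct. REDCap is described in Study design and data management as a tool for capturing data. It does not limit the chance of a false positive over repeated looks, and it makes no independent decision.
- The primary outcome counts an attempt from any source, including telephone interviews, so it is sensitive to how closely an interviewer probes.

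At stake are the false-positive rate of the primary comparison, even-handed outcome ascertainment, and confidence that the end of recruitment was not influenced by what had been seen. Knowledge gained from an effectiveness look cannot be taken back.

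**Working it through.** **Inputs.** From Power calculation: event rates of 10% (ASSIP plus usual care) and 20% (usual care), alpha 0.05, power 0.80, 15% dropout and 460 recruited. From Study design and data management: 1:1 allocation. Not stated, so assumed: two-sided testing, the total number of analyses K (including the final one) and equal spacing.

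**1. Reproduce the plan's figure.** With pooled rate 0.15,

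n = [1.960·√(2·0.15·0.85) + 0.842·√(0.10·0.90 + 0.20·0.80)]² / 0.10²
= (0.990 + 0.421)² / 0.01 ≈ 199 per group.

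This matches exactly, as a two-sided test without continuity correction. It is a fixed-sample calculation and contains no allowance for interim testing.

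**2. Is there slack?** 460 × 0.85 = 391 evaluable, against 2 × 199 = 398. Power at 391 is 79.3%. There is no reserve to absorb a stricter final level.

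**3. Type I error if every look is tested at 0.05 and any significant look can end the trial or support a claim.** Under the null, the standardised statistics at looks j < k have correlation √(j/k). The error is the probability that any of the K statistics exceeds 1.96 in absolute value. It was simulated with 1,000,000 paths and checked with binomial data (20% in both arms, 199 per arm, 200,000 runs).

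| K | Normal | Binomial check |
|---|---|---|
| 2 | 8.3% | 8.4% |
| 3 | 10.7% | 10.8% |
| 4 | 12.6% | 12.8% |
| 5 | 14.1% | 14.4% |

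If looks trigger no efficacy decision and recruitment ends on pooled dropout alone, the error is 5%.

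**4. Price of controlling the error.**

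| K | Boundary | Nominal final level | n per group for 80% power | Power at 199 per group |
|---|---|---|---|---|
| 2 | Pocock | 0.0293 | 222 | 75.6% |
| 3 | Pocock | 0.0221 | 232 | 73.4% |
| 5 | Pocock | 0.0159 | 244 | 71.0% |
| 2 | O'Brien-Fleming | 0.0480 | 201 | 79.7% |
| 3 | O'Brien-Fleming | 0.0451 | 203 | 79.4% |
| 5 | O'Brien-Fleming | 0.0413 | 205 | 78.8% |

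For K = 2 with O'Brien-Fleming, the final critical value is 1.978. The interim value at half the information is 1.978 × √2 = 2.797, a two-sided p of about 0.005.

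**5. Final number.** If the only liberty were an effect-driven choice between stopping at 398 and at 460 evaluable, the error would be about 6.7%. The article does not describe such a choice. The figure only shows what a pooled-dropout rule would prevent.

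**6. Blinding, section against section.** Outcomes says follow-up and outcome assessors are blinded. The text under Standardized evaluation forms has assessments done by project researchers, Baseline assessment has research-team members doing the interviews, and Health encounters has a research nurse doing follow-up. Overlap with those who see interim results is possible but not stated, and no barrier is described.

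**The case against.** The strongest reply is that boundaries, alpha spending and access rules normally sit in the analysis plan or full protocol, neither of which is shown, so their absence from an article proves nothing. That is right as far as it goes, and the missing boundary is not the point here. What the article does fix is who looks, that they look at effectiveness, and that a data-capture system is the reason for having no committee. An unseen plan would have to qualify those statements.

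Three stronger readings are tempting, and the text does not support them.

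- A reader might infer that the 0.05 level already fails. The stated purpose is monitoring. No stopping rule, interim claim or re-sizing rule appears, and looks that lead to no efficacy decision leave the final test at 5%.
- A reader might infer that the team may end recruitment when results look good. The sentence on fewer patients is conditional on lower dropout, and the ceiling of 460 is consistent with it. A reduction driven by pooled dropout does not inflate alpha. What remains is that people who have seen effectiveness results would apply a rule that does not say it is applied without arm data.
- A reader might infer that the blinding statement is contradicted. Nothing says that the blinded assessors run or see the interim analyses, and aggregate results do not reveal one person's allocation. It is an unaddressed risk.

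The three time windows of the primary outcome raise a separate multiplicity question, which is not counted here.

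**Conclusion.** The point stands in conditional form. The article commits the trial team to periodic effectiveness analyses during an ongoing trial, without independent review, in a design sized and tested as one analysis at 0.05. The error level is therefore not protected, and assessor blinding is put at risk.

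The possible size runs from no inflation (5%), if no look can lead to an efficacy decision, to about 8.3%, 10.7% or 14% with two, three or five unadjusted analyses that can stop the trial or support a claim. Those figures rest on an assumed number of looks, equal spacing and two-sided testing at 0.05 each time. The effect on outcome ascertainment cannot be quantified from the document.

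**What to change.** 1. In Outcomes, remove effectiveness from the purpose of the interim analyses. The team monitors safety and conduct on pooled data. Attempts and deaths are both the primary outcome and the key safety events, so any arm-level review of them should be for safety only, carry no efficacy test, and be done by someone who neither recruits nor assesses.
2. Make the one-year report in Reporting and publication plan the only comparative analysis before the 24-month analysis. State its status and alpha in advance, and keep its arm-level results from assessors still doing 24-month interviews. A blanket ban on arm comparisons until 24 months would collide with that report.
3. If an earlier effectiveness look is wanted, fix a single one in advance with an O'Brien-Fleming boundary: final level about 0.048, and power about 79.7% at 199 per group, or 201 per group to restore 80%. If the one-year report also tests efficacy, it counts as a further analysis and the boundary must cover it.
4. State that any reduction below 460 is decided on pooled dropout only, without arm data.

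The cost is mostly wording in the protocol and analysis plan, plus someone outside recruitment and assessment for arm-level safety review. The real sacrifice is that the team gives up early sight of comparative results.
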